### Variables

#### Primary and secondary outcome variables

The primary outcome variables of this study are as follows: (1) pDoC recovery, defined as emergence from MCS (eMCS), operationalized as achieving a CRS-R communication subscale score ≥2 (functional interactive communication) or a motor subscale score ≥6 (functional object use), confirmed on ≥2 standardized CRS-R assessments conducted ≥7 days apart and sustained for ≥4 consecutive weeks. This criterion applies uniformly to patients with a baseline diagnosis of VS or MCS. All recovery determinations will be adjudicated by the independent Endpoint Adjudication Committee; (2) all-cause mortality, defined as death from any cause at any point during the 5-year follow-up period (up to and including month 60). In the competing-risk analytical framework, all-cause mortality serves as the primary competing risk event for the consciousness recovery outcome. Patients who survive to the end of the 60-month follow-up without having achieved the consciousness recovery endpoint will be administratively right-censored at month 60; and (3) major cardiovascular events (MACE), encompassing myocardial infarction (defined in accordance with the Fourth Universal Definition of Myocardial Infarction, requiring elevated cardiac biomarkers in conjunction with clinical evidence of myocardial ischemia), hospitalization for heart failure (defined as inpatient admission requiring intravenous diuretics or inotropic support), and stroke (confirmed by neuroimaging [CT/MRI] with neurological deficits persisting for more than 24 h).

Secondary outcome variables include: (1) changes in functional status, assessed using the Glasgow Outcome Scale–Extended (GOS-E) and the Disability Rating Scale (DRS) (8, 9); (2) dynamic changes in biomarkers, including serum neurofilament light chain (NfL), glial fibrillary acidic protein (GFAP), S100 calcium-binding protein B (S100B), and other injury- and recovery-related biomarkers; (3) health-related quality of life, evaluated using the EQ-5D questionnaire, with caregiver proxy responses employed when direct patient assessment is not feasible; and (4) rehospitalization rate, documented by recording the frequency and causes of readmission, with particular attention to common complications such as infections, seizures, and respiratory events.

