### Follow-up procedures

Follow-up assessments will employ a hybrid surveillance strategy combining in-person evaluations with remote monitoring. Core neurobehavioral and functional assessments (CRS-R, GOS-E, DRS, EQ-5D, SF-36, FIM, HADS, and Zarit Caregiver Burden Interview) will be conducted at bedside by certified assessors at baseline and at 3, 6, 12, 24, 36, 48, and 60 months (8 assessment timepoints in total, comprising 7 in-person follow-up visits). The Chinese validated CRS-R (7) will be used throughout. Assessors must complete standardized training—covering scoring, ≥10 supervised assessments, and ICC ≥ 0.85 reliability—before independent use. The same assessor will evaluate each participant at all timepoints when feasible; if replaced, inter-rater reliability will be verified against the prior assessor’s last two evaluations. Total and subscale scores will be recorded at each visit. eMCS is defined by subscale-specific behavioral thresholds (per Primary Outcome Variables), not a total score of 23/23, which reflects full neurological recovery rather than functional communication or object use. Neuroimaging investigations (MRI/DTI/fMRI) and serum biomarkers (NfL, S100B, GFAP, and other injury-related biomarkers) will be performed at baseline and at 6, 12, 24, 36, 48 and 60 months. Following the 6-month visit, remote follow-ups will be conducted by telephone interview supplemented by caregiver-reported outcomes at 3-month intervals between scheduled in-person visits, primarily capturing vital status, rehospitalization events, and major adverse events. Remote follow-ups will be administered by uniformly trained research coordinators using standardized scripts, with video calls employed as an adjunct to confirm the patient’s general condition. In-person outpatient visits will be conducted by neurologists and rehabilitation therapists.

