Follow-up assessments will capture: changes in consciousness level (CRS-R); vital status; major cardiovascular events; functional independence (Functional Independence Measure [FIM]); health-related quality of life (SF-36); caregiver burden (Zarit Caregiver Burden Interview); changes in medication or treatment regimens; activities of daily living (ADLs) and instrumental activities of daily living (IADLs); mental health status (Hospital Anxiety and Depression Scale [HADS]); and adverse event documentation. All follow-up data will be entered in real time into an electronic data capture (EDC) system, with monthly data quality reviews conducted to achieve a target follow-up completion rate of ≥ 85%.

Outcome event ascertainment procedures are as follows: recovery status will be confirmed through a composite of clinical assessments, medical record review, and neuroimaging evidence (e.g., fMRI or EEG demonstrating improved cortical activity); death events will be ascertained via civil death registration systems, family-reported notification, and hospital records, with cause-specific mortality classified as neurological deterioration, cardiovascular events, infection, or other causes; cardiovascular events will be adjudicated according to internationally accepted definitions supported by neuroimaging and laboratory evidence. Telephone interviews have been established as a feasible follow-up modality, demonstrating agreement with self-reported outcome measures in the majority of settings, achieving a cohort retention rate of 93% within 6 months in culturally adapted intervention research, and proving applicable to the longitudinal assessment of functional and cognitive recovery trajectories following neurological infections (12) (Table 1).

**Table 1 tab1:** Evaluation parameters at baseline and follow-up visits.

Evaluation parameter	Baseline (enrollment)	Follow-up (telephone/video or on-site visits)						
	(Hospital admission)	Visit 1 (3 m)	Visit 2 (6 m)	Visit 3 (12 m)	Visit 4 (24 m)	Visit 5 (36 m)	Visit 6 (48 m)	Visit 7 (60 m)
Informed consent	x							
Inclusion criteria met	x							
Demographics & medical history	x							
Vital signs & neurological exam	x							
Consciousness level (CRS-R)	x	x	x	x	x	x	x	x
Functional status (GOS-E, DRS)	x	x	x	x	x	x	x	x
Quality of life (EQ-5D)	x	x	x	x	x	x	x	x
Survival status	x	x	x	x	x	x	x	x
Rehospitalization & complications	x	x	x	x	x	x	x	x
Adverse events	x	x	x	x	x	x	x	x

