### Multimodal prognostic prediction model construction

A multimodal prognostic prediction model will be constructed in three hierarchically nested stages: (1) a Clinical Model incorporating demographic and injury-related variables (age, sex, etiology, GCS at admission, time from injury to enrollment, and baseline CRS-R total score) selected via LASSO regression with 10-fold cross-validation; (2) a Neuroimaging-Augmented Model adding DTI-derived fractional anisotropy (corticospinal tract and corpus callosum) and resting-state fMRI default mode network connectivity to Stage 1; and (3) a Fully Integrated Multimodal Model further incorporating baseline serum biomarkers (NfL, GFAP, S100B). Model discrimination will be quantified by the C-index; incremental value across stages will be assessed using IDI and NRI (95% CIs via bootstrap resampling, 1,000 iterations). The final model will undergo bootstrap internal validation with optimism correction, and calibration will be evaluated using the Harrell calibration plot.

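### Recovery is defined and confirmed by repeated CRS-R scores in one section but confirmed with fMRI or EEG evidence in another, although fMRI connectivity is a predictor under test

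*Protocol article*

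**What the plan says.** **Definition.** In the Protocol article, Primary and secondary outcome variables, recovery is "operationalized as achieving a CRS-R communication subscale score ≥2 (functional interactive communication) or a motor subscale score ≥6 (functional object use"), and it must be "confirmed on ≥2 standardized CRS-R assessments conducted ≥7 days apart and sustained for ≥4 consecutive weeks". The section adds: "This criterion applies uniformly to patients with a baseline diagnosis of VS or MCS". An independent Endpoint Adjudication Committee decides each case. Follow-up procedures repeats the behavioural rule: "eMCS is defined by subscale-specific behavioral thresholds (per Primary Outcome Variables), not a total score of 23/23".

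**Ascertainment.** Later in Follow-up procedures, where the article explains how outcome events are established, it says "recovery status will be confirmed through a composite of clinical assessments, medical record review, and neuroimaging evidence". The imaging part is described as "neuroimaging evidence (e.g., fMRI or EEG demonstrating improved cortical activity").

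**Imaging as predictor.** Predictor variables and covariates lists DTI white-matter integrity and fMRI functional connectivity among the primary prognostic predictors. Primary analysis puts DTI-FA and fMRI default-mode connectivity into Models 4 and 5, and imaging indices into the nested comparison of recovered and non-recovered patients. Stage 2 of the prediction model adds DTI fractional anisotropy and "resting-state fMRI default mode network connectivity to Stage 1". The gain between stages is judged by IDI and NRI.

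**Blinding.** Bias control blinds outcome assessors to baseline results and calls the committee's adjudication blinded, without saying to what.

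**The concern.** Two sections use the idea of confirmation for the same primary endpoint and name different evidence. Under the first, a patient who meets the CRS-R thresholds on repeated assessments has recovered. Under the second, imaging or EEG has some part in that decision, and the part is not specified.

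This matters more than an ordinary wording conflict because fMRI is on both sides of the model. If an fMRI recording helps decide who counts as recovered, the association between the fMRI index and recovery is partly built into the outcome. The second and third of the three objectives (imaging indices as independent predictors, and a multimodal prediction model) rest on that association. The primary research question also adjusts for neuroimaging. Once events have been adjudicated with imaging in view, an analyst may not be able to recover the purely behavioural decision.

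**Working it through.** The article gives no figure for this point, so there is nothing to reproduce. The check is a comparison of the text, followed by an illustration of what could happen.

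**1. Outcome rules side by side**

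| Source | Evidence for recovery | Role of imaging |
|---|---|---|
| Primary and secondary outcome variables | CRS-R communication ≥2 or motor ≥6, repeated ≥7 days apart, sustained ≥4 weeks | none |
| Follow-up procedures, CRS-R paragraph | CRS-R subscale thresholds, referring back to the above | none |
| Follow-up procedures, event ascertainment | clinical assessments, records, imaging evidence | part of a composite; weight not stated |

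No sentence ranks one rule above the other.

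**2. Which modalities overlap**

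| Modality | Named as confirming evidence | In the listed models |
|---|---|---|
| fMRI | yes | yes (Models 4–5, nested comparison, Stages 2–3) |
| EEG | yes | no |
| DTI | no | yes |

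The circularity is shown for fMRI only.

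**3. Does baseline versus follow-up timing remove it?** The models are evidently meant to use baseline indices, while confirmation would use later recordings. Two links remain. *Improved* is a comparison with an earlier recording, so the baseline value can enter the outcome. Recordings from one patient are also likely to be correlated over time.

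**4. Can the composite be applied equally at each visit?** Table 1 assesses primary outcomes from month 3. The text schedules MRI at baseline and months 6, 12, 24, 36, 48 and 60. Table 1 has it at baseline and months 12, 24, 36, 48 and 60. So no MRI is scheduled at month 3, the two sources disagree at month 6, and the article gives EEG no follow-up times.

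**5. Illustration of direction and size.** From the documents: 34% recovery (Sample size calculation). Assumed: everything else, including that imaging is mandatory.

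- Baseline fMRI index x ~ N(0,1).
- CRS-R recovery y: logit P(y=1) = log(0.34/0.66) + log(OR)·x.
- Follow-up index f = ρx + √(1−ρ²)·e + 0.5y, with e ~ N(0,1), so recovered patients shift by 0.5 SD.
- Confirmed recovery is y together with either f > x (improved on baseline) or f > 0 (fixed level).
- 400,000 simulated patients per true OR; logistic regression of confirmed recovery on x.

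| True OR per SD | ρ | CRS-R only | Improved on baseline | Fixed level |
|---|---|---|---|---|
| 1.0 | 0.3 | 1.00 | 0.65 | 1.22 |
| 1.0 | 0.5 | 1.00 | 0.71 | 1.41 |
| 1.0 | 0.7 | 1.00 | 0.79 | 1.61 |
| 1.3 | 0.3 | 1.30 | 0.79 | 1.53 |
| 1.3 | 0.5 | 1.30 | 0.88 | 1.76 |
| 1.3 | 0.7 | 1.30 | 0.99 | 2.01 |

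The CRS-R-only endpoint returns the true value. Under either imaging rule, confirmed recovery falls from about 34% to between 21% and 25%.

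**The case against.** The best defence is that the ascertainment sentence only lists sources of information. It stands beside a similar list for deaths (registration, family report, hospital records), and the imaging item is given as an example. The outcome section already contains a complete confirmation rule, and the CRS-R paragraph refers back to it. On that reading CRS-R decides, imaging merely supports, and any bias could be small. This reading is possible, and it limits what can be said about size. It does not remove the conflict, because the article does not state it. The planned sensitivity analysis with alternative recovery criteria does not settle which definition is primary either.

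A reader might also infer more than the text supports:

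- *The fMRI effect and the Stage 2 gain will be inflated.* Not established. If improvement is judged against baseline, the illustration shows attenuation or reversal.
- *All imaging predictors are affected.* DTI is not named as confirming evidence, EEG is in none of the listed models, and EEG may serve in place of fMRI.
- *A recovery at month 3 cannot be confirmed.* EEG is allowed and its follow-up timing is not fixed, and a later scan is possible. Unequal opportunity across visits stands; impossibility does not.
- *The committee will see baseline scans.* Two radiologists review all imaging and could report change alone. The article does not say what the committee receives.
- *The bias can be set against the planning hazard ratio of 1.3.* That would need confirmation rates by fMRI status, which the documents do not give. The planning ratio also concerns an exposure with 30% prevalence, and the primary exposure is baseline consciousness level, not an imaging index.

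**Conclusion.** The point holds in a limited form. The article gives two accounts of how the primary recovery endpoint is confirmed and does not reconcile them. Following the ascertainment sentence as written lets fMRI, a predictor modality under test, influence the outcome that it is meant to predict. That is incorporation bias for the fMRI index.

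Its size and direction cannot be determined from the documents. It could be small if imaging is only supportive. If imaging is mandatory, the assumed scenarios run from an apparent odds ratio of 0.65 to one of 1.61 when the truth is 1.0, and from 0.79 to 2.01 when the truth is 1.3. These figures show only that the unstated rule can decide the answer; they are not estimates for this cohort. The uneven imaging schedule adds a second problem: if imaging counts, the chance and timing of confirmation would depend on the visit and on whether the patient can be scanned.

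**What to change.** In the event-ascertainment paragraph of Follow-up procedures, remove neuroimaging and EEG from the confirmation of recovery. State that the Endpoint Adjudication Committee decides recovery by the CRS-R criterion in Primary and secondary outcome variables, with clinical records in support, and is blinded to all imaging and EEG results. Say the same in Bias control, where the content of the committee's blinding is now open. Report imaging change in recovered patients as descriptive data.

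Biomarker results need no new rule on this account, because the ascertainment sentence does not use them. The month 6 imaging entry in Table 1 should still be reconciled with the text, but with this change it no longer bears on the endpoint.

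The cost is about one sentence in the protocol and matching wording in the committee's working rules, with no added procedures. It should be done before enrolment opens, planned for June 2026.

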### Bias control

To minimize selection bias, a systematic three-step recruitment procedure (screening, informed consent, and baseline assessment) will be implemented with independent review by a multidisciplinary team. To address follow-up bias, a hybrid surveillance strategy combining telephone interviews and outpatient visits will be employed, with a target follow-up completion rate of ≥ 85% and active tracing of participants lost to follow-up. Confounding bias will be controlled through multivariable regression models incorporating documented potential confounders, with effect modification explored in prespecified subgroup analyses. To mitigate performance and detection bias, outcome assessors will be blinded to baseline results; all primary outcome events will be adjudicated by an independent Endpoint Adjudication Committee in a blinded manner; and all neuroimaging data will be independently reviewed by two radiologists. The study has been prospectively registered on an international clinical trial registry and will be reported in accordance with the STROBE statement.

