### Sample size calculation

The sample size was determined based on 5-year consciousness recovery rates reported in the existing literature on prolonged disorders of consciousness. Chen et al. (13) reported a 5-year consciousness recovery rate of 42.3% in a prospective cohort of Chinese patients; a systematic review by Giacino et al. (14) indicated recovery rates of approximately 35–50% among patients with pDoC following TBI; and a recent longitudinal study by Yan et al. (15) reported a 5-year cumulative recovery rate of 48.7%. Given that the present study enrolls a mixed-etiology cohort (traumatic and non-traumatic) and employs a competing-risk analytical framework, a conservative 5-year cumulative incidence rate of 34% (annual event rate: 8%) was adopted as the basis for sample size estimation, ensuring adequate statistical power. Assuming a hazard ratio (HR) of 1.3, two-sided *α* = 0.05, 80% statistical power, and an exposure proportion of 30%, the required number of events was calculated as 544 using the Schoenfeld formula. Adjusting for an anticipated 15% loss to follow-up over the 5-year period, the target sample size was determined to be 1,000 participants. This sample size will ensure adequate statistical power for the primary survival outcome, support detection of secondary outcomes (functional recovery and quality-of-life changes), enable the identification of moderate effect sizes (Cohen’s *d* ≥ 0.5 or OR ≥ 1.5), and accommodate prespecified subgroup analyses. Prespecified subgroup analyses will evaluate the influence of age, sex, and baseline severity; assuming a subgroup prevalence of 30% and an event rate consistent with the overall cohort, ≥ 80% power will be achievable for detecting HR ≥ 1.5 within each subgroup.

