### Loss to follow-up

A standardized definition of loss to follow-up will be applied (three consecutive missed follow-up contacts). Data from participants lost to follow-up will be right-censored at the time of their last valid contact. Reasons for loss to follow-up (relocation, withdrawal, death, loss of contact, etc.) will be systematically documented. Baseline demographic and clinical characteristics will be compared between participants lost to follow-up and those who complete follow-up to assess potential selection bias. Inverse probability weighting (IPW) will be applied as needed to statistically correct for informative censoring due to dropout, thereby enhancing the external validity and generalizability of study findings.

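### No common censoring date is set for all-cause mortality: registry deaths can count to month 60, while lost participants are censored at last contact

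*Protocol article*

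**What the plan says.** Three statements in the protocol article bear on when a participant stops being followed for death.

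- **Endpoint** (Primary and secondary outcome variables): the mortality outcome is "death from any cause at any point during the 5-year follow-up period (up to and including month 60"). Death is also the competing event for recovery.
- **Source** (Follow-up procedures): "death events will be ascertained via civil death registration systems, family-reported notification, and hospital records". The first of these sources works without study contact.
- **Censoring** (Loss to follow-up): loss means "three consecutive missed follow-up contacts", and "Data from participants lost to follow-up will be right-censored at the time of their last valid contact". No outcome is exempted. The same section lists death among the possible reasons for loss.

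The article does not say whether a death found in the registry after last contact is an event. It also does not say to what date a lost participant with no death record is carried as alive. The sample size section anticipates 15% loss over 5 years.

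**The concern.** Deaths and survivors need the same observation window. Here the window for deaths can run to month 60 through the registry, while the window for survivors who lose contact closes at the last contact. A participant lost at month 12 would then appear in the later risk sets only if he or she goes on to die. That is outcome-dependent follow-up, and it biases Kaplan-Meier and Cox estimates however large the cohort.

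Closing both windows at last contact avoids this, but it drops deaths that the endpoint definition includes and that the study may already know of.

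Recovery has a related problem. It needs repeated CRS-R assessments, which stop when contact stops, whereas death can still be seen. A participant who recovers unobserved and later dies would be coded as dead without recovery.

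**Working it through.** **Plan's own figure.** The article gives no mortality figure to reproduce. Its one derived figure, 544 events, is confirmed: (1.960 + 0.842)² / (0.3 × 0.7 × (ln 1.3)²) = 543. It bears only indirectly on this point.

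**Inputs from the article.** Loss of 15% over 5 years; horizon 60 months; 1,000 participants.

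**Assumptions not in the article.** Annual mortality a of 5%, 10% or 15%, constant over time. Loss at a constant rate, unrelated to death, with the 15% read as the probability of loss by year 5 in the absence of death. A complete registry unless stated.

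**Set-up.** λ = −ln(1 − a) = 0.0513, 0.1054, 0.1625. γ = −ln(0.85)/5 = 0.0325. S(t) = exp(−λt) and G(t) = exp(−γt). True 5-year mortality is 1 − S(5).

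**Reading A: registry deaths count, lost survivors are censored at last contact.** The risk set at t holds everyone who will die between t and year 5, S(t) − S(5), plus survivors still in contact, S(5)G(t). The apparent hazard is λS(t) / [S(t) − S(5)(1 − G(t))], and the estimate is 1 − exp(−its integral from 0 to 5). If the registry finds a share r of post-loss deaths, the event density and the S(t) − S(5) term are both multiplied by G(t) + r(1 − G(t)).

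**Reading B: everyone lost is censored at last contact, deaths included.** With non-informative loss the estimate equals the truth. Deaths retained are λ/(λ + γ) × (1 − 0.85·S(5)). Person-time retained is (1 − 0.85·S(5))/(λ + γ), against (1 − S(5))/λ with full follow-up.

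| Annual mortality | 5% | 10% | 15% |
|---|---|---|---|
| True 5-year mortality | 22.6% | 41.0% | 55.6% |
| A: excess, complete registry | +1.5 | +2.2 | +2.3 |
| A: excess, half of post-loss deaths found | +0.8 | +1.1 | +1.2 |
| A: person-time lost | 6.8% | 5.9% | 5.0% |
| B: bias, non-informative loss | 0 | 0 | 0 |
| B: deaths discarded per 1,000 | 17 | 29 | 37 |
| B: person-time lost | 7.4% | 7.0% | 6.7% |

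Excesses are in percentage points.

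**Sensitivity of reading A** (complete registry). At 5% loss the excess is 0.5 to 0.7 points; at 25% loss it is 2.8 to 4.1. If all 15% were lost just after baseline, the estimate would be m/(m + 0.85(1 − m)) for true mortality m. With m = 40% this is 0.40/0.91 = 44.0%, an excess of 4.0 points.

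**Informative loss under reading B.** Suppose mortality doubles after loss (assumed). True mortality is then 1 − [0.85·S(5) + ∫γ·exp(−γu)·exp(−λu)·exp(−2λ(5 − u))du], with u from 0 to 5. Reading B understates it by about 1.4 to 2.1 points.

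**The case against.** The strongest reply is that the upward bias needs a mixture that the article never states. Taken literally, the loss-to-follow-up rule covers all data of a lost participant, so it closes deaths and survivors together. The ascertainment sentence names sources only and does not say that later deaths override censoring. This stands, and it makes the overstatement conditional. It does not make the text consistent, because the literal rule then removes deaths that the endpoint definition counts.

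The article also gives no registry coverage, no plan to link every participant and no month-60 query. Complete vital status cannot be assumed, and carrying everyone without a death record to month 60 would understate mortality if deaths go unrecorded. This stands too, and the fix needs a safeguard for it.

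The size is modest. At 40% mortality and 1,000 participants, the 95% half-width is 1.96 × √(0.4 × 0.6/1,000) = 3.0 points even without censoring. But the bias does not shrink with sample size.

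The article plans active tracing, and says that "Inverse probability weighting (IPW) will be applied as needed to statistically correct for informative censoring due to dropout". Tracing lowers the loss but sets no common date. Weighting can help under the literal reading if measured covariates explain the loss. It cannot repair the mixed reading, where censoring depends on surviving to month 60.

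Finally, endpoint-specific censoring dates are often left to the analysis plan. Mere silence would not be a finding. Here, however, the article states a rule, and that rule conflicts with its own endpoint definition.

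**Conclusion.** The point holds in conditional form. The endpoint, the death sources and the loss rule set no common censoring date for mortality, and each way of combining them has a cost.

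- If post-contact registry deaths count, which fits the endpoint definition best, 5-year mortality is overstated by about 1.5 to 2.3 points at 15% loss with a complete registry, or 0.8 to 1.2 points if half of those deaths are found.
- If the loss rule applies to everyone, there is no upward bias under non-informative loss. About 17 to 37 deaths per 1,000 and about 7% of person-time are discarded, and mortality is understated if it rises after loss.

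All sizes rest on the assumed mortality rates and the constant, independent loss.

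A reader might infer that the plan simply overstates mortality; the literal loss rule does not support that. A reader might also infer a distorted VS vs MCS mortality hazard ratio. That arises only if loss differs between the groups, which the article does not state. As an illustration, a true ratio of 1.0 becomes about 1.05 to 1.08 under the mixed reading if loss is assumed to be 25% in VS and 11% in MCS. For recovery the direction of the misclassification is clear, but no size was derived.

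**What to change.** In the loss-to-follow-up section:

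1. Exempt all-cause mortality from last-contact censoring. Query the civil registry for all linkable participants at month 60 or at one fixed linkage date, count deaths to that date, and censor those without a death record at the same date.
2. Censor participants who cannot be linked at last contact. If registry coverage proves incomplete, censor deaths and survivors alike at last contact, as the primary or a sensitivity analysis.
3. For recovery, close recovery and competing death together at the last CRS-R assessment of a lost participant. Add a sensitivity analysis that counts later registry deaths as competing events.
4. State that a known death is an outcome event, not a reason for loss, under the date rules above.

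The cost is a few sentences and one registry query, using a source the article already names. The downsides are registry reporting lag, which a fixed linkage date can allow for, and understated mortality if the registry misses deaths, which item 2 is there to guard against.
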